### Primary outcome measures

The objectively and subjectively measured difference in nocturnal restlessness between T0-T1-T2. Objectively, the nocturnal restlessness measured during six weeks by means of an actiwatch validated for sleep research with the sleep/wake parameters mentioned above.

Subjectively, nocturnal restlessness determined on the basis of a sleep diary developed for this study, and filled in by the nursing staff.

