### Sample size

In this study, it is assumed that the nocturnal restlessness in patients in the control group will remain stable, with a frequency of 80% episodes of nocturnal restlessness [18]. By applying PAS therapy, a conservative decrease of nocturnal restlessness of 30% is expected, resulting in a restlessness frequency of 50%. Taking into account a probability value of 5% (alpha), a power of 80% (1-beta), and a drop-out rate of 10%, 66 patients are needed in total, that is 33 in the intervention group and 33 in the control group.

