### Randomization

By means of blinded block randomization with group sizes of six, the randomization scheme will determine which patients will be placed in the intervention group and the control group. The intervention is not blinded because it is visible for the caregiver (box with computer below the bed and faintly audible (a very low buzz).

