### Statistical analysis

In order to process the data to test our hypothesis, the statistical software programme SPSS-19 [34] will be used. First, data will be checked for missing values and normal distribution. It will be examined whether there is a significant difference in both nocturnal restlessness and degree of neuropsychiatric symptoms between the intervention group and the control group.

To analyze the actigraphy variables and the variables measured by means of NPI-NH (T0, T1, and T2) integrally, a multilevel regression model (Mixed Models) will be used. In this study, the Basic Two-Level Regression Model [35] will be used, in which the actigraphy variables and NPI-NH variables are the lowest levels (that is dependent variable) and the research participants the highest level (independent variable).

The multilevel analysis enables us to calculate the degree of nocturnal restlessness and neuropsychiatric symptoms despite the unequal number of observations per individual (missing values/dropouts). This means that all data will be included in the analysis, including the data of participants who will meet stop criteria during the investigation and for whom the study has to be terminated early.

If there is interaction effect between time and group, a post-hoc analysis will be performed, taking into account that T0-T1 indicates PAS therapy effects and that T1-T2 indicates the long-term effects of PAS therapy. The analyses will be corrected for basic differences in the characteristics of the patients belonging to the intervention group and the control group respectively. The data in the sleep diaries will first be coded and later analyzed separately by means of describing statistics.

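### Five actigraphy parameters and a staff diary are all primary for one hypothesis, with no rule for which decides, and the diary is only described

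*Protocol article*

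**What the plan says.** Under General objective there is a single hypothesis: PAS therapy will significantly reduce nocturnal restlessness.

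Under Primary outcome measures, that one concept has two halves, both compared over the three two-week periods. The first is "Objectively, the nocturnal restlessness measured during six weeks by means of an actiwatch validated for sleep research with the sleep/wake parameters mentioned above". The list it points to, under Data collection, has five entries: (1) mean night-time motor activity, which the article itself labels nocturnal restlessness; (2) sleep efficiency; (3) wake bouts; (4) inter-daily stability; (5) intra-daily variability. The second half is "Subjectively, nocturnal restlessness determined on the basis of a sleep diary developed for this study, and filled in by the nursing staff".

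Secondary outcome measures covers neuropsychiatric symptoms only, so none of the five parameters is ranked lower there.

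Statistical analysis enters the actigraphy variables, in the plural, as dependent variables in a two-level mixed model. Post-hoc contrasts follow only if there is an interaction between time and group. The T0-T1 contrast is said to reflect the therapy effect and T1-T2 the longer-term effect. For the diary: "The data in the sleep diaries will first be coded and later analyzed separately by means of describing statistics". On masking, Randomization says: "The intervention is not blinded because it is visible for the caregiver".

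**The concern.** One hypothesis is attached to five tested measures and one untested measure. The plan does not say whether one, any or all must succeed. Read as written, significance on any of the five could be reported as support for the hypothesis, and the parameter carrying the claim could be chosen after the data are seen.

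The diary raises a separate problem. It has primary status but no test, so it can neither confirm nor refute the hypothesis. It is also completed by staff who can know the allocation. If diary and actigraphy disagree, the article gives no way to resolve it.

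An analysis plan that is not shown may hold the details of alpha allocation. Naming the primary outcome is a protocol matter, though, and this article addresses it and leaves it plural.

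**Working it through.** **1. Does the sample size show which measure decides?** Inputs from Sample size: control frequency 80% ("with a frequency of 80% episodes of nocturnal restlessness"), intervention frequency 50%, alpha 5%, power 80%, drop-out 10%, total 66. A one-sided 5% test with unpooled variance reproduces the total:

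- n per arm = (1.645 + 0.842)² × (0.8×0.2 + 0.5×0.5) / 0.30² = 28.2, rounded up to 29
- 29 / 0.9 = 32.2, rounded up to 33 per arm, 66 in total

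The article does not state sidedness, and two-sided variants give 80 to 100 in total. For this point, what matters is that the calculation covers one binary comparison at one alpha. A frequency of restless episodes is none of the five listed parameters, so the calculation does not identify the deciding one.

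**2. Count of tests.** There are five actigraphy parameters. The diary is not tested, so the count is five, not six.

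**3. Claim rule A: a significant interaction on any of the five.** For independent tests, 1 − 0.95⁵ = 0.226. The article gives no correlation between parameters, so a common correlation is assumed and varied. With three periods the interaction has 2 degrees of freedom. Write d0, d1, d2 for the between-group differences in the three periods, each with period-specific error SD σ; under compound symmetry the shared patient term cancels. The interaction is significant if Σ(d_t − mean d)² / σ² > 5.99. Simulated with no true effect:

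| Correlation between parameters | 0 | 0.5 | 0.7 | 0.9 |
|---|---|---|---|---|
| At least one false interaction | 22.5% | 18.6% | 15.2% | 10.4% |
| Multiple of 5% | 4.5 | 3.7 | 3.0 | 2.1 |

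Unequal correlations, with the three night parameters more closely related to each other than to the two rhythm parameters, give 15.0% to 19.8% (simple two-sided tests).

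**4. Claim rule B: a significant interaction and a significant T0-T1 contrast on the same parameter.** This follows the order in Statistical analysis. The contrast is significant if |d1 − d0| / (σ√2) > 1.96 and is looked at only when the interaction is significant.

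| Correlation between parameters | 0 | 0.5 | 0.7 | 0.9 |
|---|---|---|---|---|
| Five parameters, at least one false claim | 12% | 10% | 8% | 5% |
| One parameter, same rule | 2.5% | 2.5% | 2.5% | 2.5% |

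The multiple from having five parameters is therefore 5/2.5 = 2 to 12/2.5 = 4.8. If only a decrease counts, all these rates are about halved: roughly 6%, 5% and 4% at correlations 0, 0.5 and 0.7, against about 1.2% for one parameter.

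**5. The diary.** Primary outcome measures makes it one half of the primary outcome. Statistical analysis gives it descriptive statistics only. As it stands it has the label of a primary outcome and the analysis of a supportive one.

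**The case against.** Four counter-arguments deserve an answer.

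- **Parameter (1) already carries the name.** This makes it the natural choice, but both Data collection and Primary outcome measures tie restlessness to the whole set, so it has not been chosen.
- **The analysis is described as integral, which could mean one joint test.** The named model is a basic two-level regression, and it is not described as a joint test across outcomes.
- **The post-hoc step is gated.** This stands and limits the size. A reader might count two contrasts for each of five parameters and quote ten tests, with 40%, 29% and 21% at correlations 0, 0.5 and 0.7. The plan does not support that: the contrasts run only after an interaction, so the five interaction tests cap the chance of a false claim.
- **The diary already works as supportive information.** Data collection says it complements the actigraphy, and the Discussion acknowledges its limits. This largely stands; what is left is a primary label that its analysis does not match. A reader might also infer that the person who switches on the mattress writes the diary. The article says only nursing staff for both tasks, so what is established is lack of blinding.

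It is also tempting to say that inter-daily stability and intra-daily variability do not belong because they are not night measures. The Background counts disturbance of the day/night rhythm as a form of nocturnal restlessness, so that criticism fails. Their place in the list is defensible; their equal primary rank without a deciding rule is the problem.

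**Conclusion.** The point holds in this form. Five actigraphy parameters and a diary are all primary for one hypothesis with no deciding rule, and the diary's primary status conflicts with its purely descriptive analysis.

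The size depends on two things the article does not fix. If any significant interaction counts, the false-positive chance is about 10% to 23%, and about 15% to 19% at correlations of 0.5 to 0.7. If the T0-T1 contrast must also be significant, it is about 5% to 12% two-sided, against about 2.5% for a single parameter. Under that stricter rule the absolute rate can sit near 5%, although it is still at least double what one parameter would give.

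A reader might state flatly that the error is three to four times 5%. That holds only for the any-interaction rule with correlations of about 0.4 to 0.7. Nor does the diary contribute to the inflation. The calculations assume a common correlation, compound symmetry over the three periods and large-sample tests.

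**What to change.** Under Primary outcome measures, name one deciding outcome. Parameter (1), night-time motor activity, is the natural candidate because the article already labels it nocturnal restlessness and the hypothesis uses that term. Make the between-group contrast in change from T0 (weeks 1-2) to T1 (weeks 3-4), taken from the planned mixed model, the deciding comparison. Give the weeks explicitly, because Table 1 uses the T labels differently from the text.

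State how activity recorded in the 30-minute vibration window is handled, identically in both arms. Data collection plans a control actimeter to see whether the device responds to the mattress itself. Any such response would affect this parameter in the intervention arm only.

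Make the other four parameters secondary and relabel the diary as supportive, descriptive information.

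The cost is wording in the protocol and analysis plan, with no added data collection. The downside is that a positive result on another parameter or in the diary can no longer carry the main claim. The change also does not reconcile the 80% versus 50% planning rates with a motor-activity outcome; the Sample size section would still need to address that.

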### Secondary outcome measures

The secondary outcome measure in this study involves an analysis of the prevalence and the degree of change in overall neuropsychiatric symptoms of the nursing home patients taking part in the study.

## Discussion

In general, professionals and informal caregivers often face considerable difficulties in solving behavioral problems present in demented people. In this study we focus on the problem of nocturnal restlessness, often leading to a diminished quality of life of the patients involved, and sometimes a severe burden for the patient's environment. Attempts to solve this problem adequately and safe with medication have proven to be hardly effective or not effective at all [5].

That is the most important and underlying reason for research on the effectiveness of non-pharmacological interventions. This study about the effectiveness of the PAS therapy, a non-pharmacological treatment option for nocturnal restlessness in demented people, is an example of this type of studies. PAS therapy is safe and patient-friendly and has not led to undesired side effects or reports of adverse effects in other applications.

The design chosen for this study has some limitations. For instance, it is not possible to carry out a double-blinded study, as the PAS mattress involves a light buzzing and is controlled by a computer that is built in the night table next to the bed.

However, given the setting and the nature of the group of residents, the risk of contamination can be considered to be small.

Furthermore, actigraphy is particularly suitable for measuring nocturnal restlessness, but less suitable for measuring periods during which the patient lies awake quietly [27].

In addition, it must be noted that when it comes to writing down data in the sleep diaries, the researchers depend on the nursing staff's compliance. Therefore, the nursing staff has received explicit instructions, and the researchers regularly check whether these instructions are being followed. Nevertheless, in daily practice of nursing home care, it is impossible to completely take into account all relevant factors.

Despite these limitations, if proven effective, this form of PAS therapy can be widely introduced in a simple and relatively inexpensive manner in order to reduce nocturnal restlessness in demented people. The therapy can be applied in institutions, for example nursing homes and residential homes for the elderly, as well as at home.

Ultimately, this may lead to a decrease in the frequent and still common use of often harmful psychotropic drugs.

In a more general sense, the care needs of demented people may decrease as well as the number of preventable admissions to care institutions [36].

## Trial status

The study started recruiting participants in July 2011. This is still ongoing. Soon after the first recruitments, the interventions and the measurements started as well. We expect the results to be published at the end of 2013.

## Abbreviations

BANS-S: Bedford Alzheimer nursing severity scale; BOPZ: Wet bijzondere opnemingen in psychiatrische ziekenhuizen (Psychiatric Hospitals Compulsory Admissions Act); CIRS: Cumulative illness rating scale; NPI-NH: Neuropsychiatric Inventory - Nursing home version; PAS: Therapy Physio Acoustic Sound therapy; PSG: Polysomnography; WMO: Wet medisch-wetenschappelijk onderzoek met mensen (Medical Research Involving Human Subjects Act).
